#### Qualitative feedback

Semi-structured interviews exploring participants’ and coaches’ experiences of the SHAPE intervention. This complementary study aims to collect constructive feedback from participants and coaches about the perceived acceptability, accessibility, and suitability of SHAPE to guide improvements. Approximately 20 participants and 5 coaches will be individually interviewed remotely (by a phone call or by audio link on Microsoft Teams), with interviews lasting up to 1 h. The interviews will be audio recorded with participants’ consent and transcribed verbatim. Data of interest will focus on what worked and what worked less well from the provider’s and receiver’s point of view. Interview questions will be designed and developed with the help of PPIE and will include questions about the training, coaching, tools used, online modules, accessibility, feasibility, and suitability of SHAPE. Interviews conducted with trial participants will occur during the period between participants completing the SHAPE intervention and receiving their 6-month follow-up. Interviews with wellbeing coaches will take place during the period that coaches are delivering the SHAPE intervention, or shortly afterward.

### Plans to promote participant retention and complete follow-up {25b}

To support retention and prevent dropouts, participants and prospective participants will receive a £10 e-voucher as an honorarium for each SCID-5 assessment they complete (4 assessments for the waitlist condition, 3 assessments for the intervention condition, and 1 assessment for prospective participants found to be ineligible). Participants will be able to spend their e-voucher on a variety of brands.

Participants are allowed to withdraw at any stage of the trial and ask for their data to be deleted. Their future treatment in NHS and private services will not be affected by withdrawing from the study. Withdrawal after randomisation will be recorded along with reasons (if provided). Participants who withdraw from the intervention or waitlist condition will continue to be sent follow-up questionnaires unless they withdraw their consent for this.

Participants who do not respond to initial invitations to take part in SCID-5 assessments will be contacted using a variety of available approaches (email, phone call, SMS) unless they have withdrawn their consent from the trial. Participants who are reluctant to complete the longer questionnaires or the SCID-5 assessments at 4 weeks post-random allocation, 8 weeks post-random allocation, or 6 months post-intervention completion will be sent the PCL-5 and PHQ-9 as a minimum dataset.

### Data management {26}

The trial will comply with the Data Protection Act that requires research data to be pseudonymised as soon as it is practical to do so. The research team will ensure that participant confidentiality is maintained and protected. Participants will each be assigned a four-digit unique identifier to protect their privacy. This unique ID will be attached to all participant outcome data instead of using the participant’s personal information. A linkage list connecting personal data (i.e. name, email address, mobile number, Trust, occupation, and referral pathway) to unique ID will be kept separate from the trial data and will be safely stored in a separate folder on a 2-factor authenticated restricted access file on the University’s secure storage space, Nexus 365 OneDrive for Business, that only the trial lead will be able to access.

Once a participant has completed the trial, and all data have been analysed, personal data (first and last name, age, index event, employment organisation, and health economics information) including contact details (unless the participant gives permission for us to retain these) and any identifiable information about physical and mental health will be destroyed.

Participants’ electronic consent forms will be uploaded securely and stored in a separate file on Nexus 365 OneDrive for Business. Records of consent will be retained for a minimum of 3 years after the end of the research study. If participants complete a telephone assessment, the audio recording will be uploaded onto Nexus 365 OneDrive for Business, and the original recording will be deleted. These recordings will be stored securely until participants have completed the study and their data have been analysed. The recordings will then be permanently deleted.

Raw outcome data (questionnaires, consent forms, screening measures) uploaded to Outlook 365 for Business will be protected. Outlook 365 for Business uses a 2-factor authentication method and is secure. Additionally, the University of Oxford implements up-to-date procedures to keep its accounts well protected and safe.

Raw data stored on Qualtrics will be protected through Qualtrics high-end security measures as well as using a secure password that will be generated by a high-end password manager. Qualtrics is a highly secure software platform that prioritises the protection and safety of customer data. Qualtrics servers are protected by high-end firewall systems and Qualtrics uses Transport Layer Security (TLS) encryption for all transmitted data. Once the final data have been analysed and the study is complete, all questionnaires and participant data on Qualtrics will be destroyed.

An interim analysis will be conducted during the trial to allow for the primary and secondary analyses (excluding the 6-month analyses) to be conducted, written up, and presented in a DPhil thesis. This thesis will be embargoed for 3 years. Due to the trial being deemed to be low risk, this interim analysis will not dictate how the rest of the follow-up is performed and will not result in the trial being terminated. For the interim and final statistical analyses, the pseudonymised data will be downloaded from Qualtrics and stored on a password-protected file on Nexus 365 OneDrive for Business. Data files downloaded from Qualtrics will be cross checked to ensure that the number of rows (participants) and columns (questionnaire items) matches the original number of submissions and questionnaire items respectively, on Qualtrics. Changes made to the trial data will be logged in an audit log. The final data files of the anonymised data will be available to the research team, principal investigator, and health economist.

De-identified research data will be stored on Nexus 365 OneDrive for Business for the duration of the trial. De-identified data will be stored here for 3 years after the end of the research project and then will be permanently deleted.

## Statistical methods

### Statistical methods to compare groups for primary and secondary outcomes, including harms {27a and 27b}

Consistent with the BMJ and Consolidated Standards of Reporting Trials guidelines, all analyses will be intent-to-treat (ITT) from randomisation, whereby participants will be analysed under the same conditions as they were randomly assigned, irrespective of the treatment they actually received, subsequent willingness, adherence, or completion of follow-up outcome measures. Primary and secondary main trial analyses will be conducted once all willing participants in both conditions have completed their 8-week post-random allocation SCID-5 assessment and questionnaires. Follow-up analyses will be conducted at the conclusion of the trial period (i.e. after all willing participants in both conditions have completed their 6-month post-intervention follow-up SCID-5 assessment and questionnaires).

#### Main trial analyses

##### Primary outcome

The primary outcome measure will be SCID-5 diagnosed PTSD and MDD at 8 weeks post-random allocation. The primary outcome measure will be analysed using logistic regression. The outcome will be a binary outcome measure whereby, if a participant meets diagnosis for one or both disorders (PTSD and/or MDD), they will score a 1 (present), whereas if a participant does not meet diagnostic criteria for either disorder, they will score a 0 (absent). All participants will begin the trial with a score of 1 since they will have a diagnosis of PTSD and/or MDD at the outset, consistent with eligibility criteria.

Where the primary outcome is measured at one time point, it has been shown that logistic regression is valid with a data missing at random assumption [66]. Complete case analysis will be conducted if missingness is <5%, whereby participants with missing data will be excluded from the primary analysis. Multiple imputation will be conducted as a sensitivity analysis for the primary outcome if missingness is >5% to check for robustness of results.

Models will include fixed factors of condition (SHAPE, waitlist). The stratification variables absence/presence of PTSD assessed with the SCID-5 at baseline, depression symptom severity (<15 or 15) assessed at baseline with the PHQ-9, and time since reported trauma (>/<18 months) assessed at baseline with the PCL-5 will be included as fixed covariates. The significance level will be set to *p* < 0.05 for comparison between the SHAPE and waitlist conditions.

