### Trial design {12}

The trial is a randomised controlled superiority single-blind trial with two parallel conditions using a 1:1 allocation ratio. Participants and coaches will not be blind to participants’ condition allocation due to the nature of the interventions. Assessors collecting primary and secondary outcome measures at 8 weeks post-randomisation and 6 months post-intervention follow-up will be blinded to the trial arm.

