### Sample size {19}

The sample size for the randomised controlled trial was calculated based on 90% power, at a significance level (*α*) of 0.05, to detect a difference in proportions of the number of participants continuing to have PTSD and MDD at 8 weeks post-random allocation. An anticipated recovery rate of 50% of participants in the intervention condition (i.e. 50% not recovered) and 16% of participants in the waitlist condition (i.e. 84% not recovered) corresponds to a relative risk of 0.59, requiring 39 participants per condition (78 in total). Allowing for up to 15% attrition increases the required sample size to *N* = 92 (46 participants per condition).

The effect size (50% recovery) for the intervention condition was informed by the NHS Talking Therapies target of 50% recovery for all individuals completing treatment [36]. This is a conservative estimate as findings from the pilot study of SHAPE comparing participants scores on the PCL-5 and PHQ-9 found recovery rates of 77.1% and 64.3% for MDD and PTSD respectively ([name], [name], Wilkins A, Storch C, Browne H, & [name]. Cognitive therapy coaching for PTSD and depression symptoms in healthcare workers repeatedly exposed to trauma: a pilot evaluation of SHAPE, under review). We chose a 50% recovery rate in line with the NHS Talking Therapies target and to allow for greater power for the secondary analyses. The effect size (16% recovery) for the waitlist condition was based on previous studies documenting natural recovery rates for PTSD and MDD over a 2–3-month period of between 12 and 20% for both disorders [37–40]. The 15% attrition estimate was based on dropout rates of similar trials and studies reporting rates of between 10 and 20% [37, 41–47].

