## Methods: assignment of interventions

### Randomisation

#### Sequence generation {21a and 21b}

After completing the telephone assessment, the second consent form, and the baseline questionnaires, participants will be randomised to one of two conditions (SHAPE or waitlist condition) on a 1:1 ratio. Randomisation will be conducted using the computer software programme Minim [55] by an independent researcher, separate to the main research team to minimise potential researcher bias. The software uses a minimisation method, and participants will be randomised based on 3 potential prognostic factors (absence/presence of PTSD using the SCID-5, depression symptom severity on the PHQ-9 (<15 or 15), and time since trauma (>/<18 months) on the PCL-5). We chose to use a median split of 15 for MDD severity using the PHQ-9 based on our pilot study where the median score on the PHQ-9 for people who were diagnosed with MDD using the SCID-5 was 15. This decision is consistent with a recent research study that dichotomised participants on the PHQ-9 with 0 for those scoring <15 or 1 for those scoring 15 or more [56]. For participants who have not experienced a traumatic event in their lives and/or do not meet criteria for PTSD, they will be asked to complete the PCL-5 in relation to the most stressful event that currently bothers them the most, indicating when this occurred. This event will be used for the time-since-trauma prognostic factor.

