##### Secondary outcomes

All secondary outcome analyses will be treated as exploratory analyses.

Between-group analyses of the continuous secondary outcome measures will include mixed effects regression models and multiple regression models following the same specifications as the primary outcome measure with additional fixed effects for time, a time by condition interaction, and a random effect for participant for the mixed-effect regression models. Mixed effects regression models allow for the inclusion of all available data from randomised participants (ITT), can account for missing data, and can account for repeated measures [67]. Between-group effect sizes (Cohen’s *d*) will be calculated by dividing the adjusted group difference by the baseline standard deviation.

For secondary outcome measures collected at 4 and 8 weeks post-random allocation (i.e. PCL-5, PHQ-9, GAD-7, PTCI-s, and RIQ-s), statistical models of treatment effects will include categorical fixed factors of time (4 weeks, 8 weeks post-random allocation), condition (SHAPE, waitlist), and the time × condition interaction. The interaction permits the estimation of differences between treatments at each timepoint. Participant will be treated as a random effect to account for between-participant variation.

For secondary outcome measures collected at 8 weeks post-random allocation only (i.e. ISI, ITQ, WEMWBS, CD-RISC, and social support scales), we will fit multiple regression models including condition (SHAPE, waitlist).

The stratification variables absence/presence of PTSD assessed with the SCID-5 at baseline, depression symptom severity (<15 or 15) assessed at baseline with the PHQ-9, and time since reported trauma (>/<18 months) assessed at baseline with the PCL-5 will be included as fixed covariates, along with the baseline score of the measure being analysed. Significance level will be set to *p* < 0.05 for comparison between the SHAPE and waitlist conditions.

To assess for potential correlates of PTSD and MDD symptom change, we will conduct correlational analyses to assess the strength of the relationship between change in posttraumatic cognitions and maladaptive responses to intrusions from baseline to week 4, and from baseline to week 8 and change in PTSD and MDD symptom severity over the same time periods, controlling for baseline scores on these measures. This analysis will be conducted with the whole sample at week 8 to include post-intervention and post-wait participants.

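### The primary logistic model is valid but makes inefficient use of baseline severity: PHQ-9 enters only as a split at 15 and the PCL-5 score not at all

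*Protocol article*

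**What the plan says.** Under Main trial analyses, Primary outcome, the protocol article fixes a logistic regression of a binary SCID-5 outcome (either disorder present, or neither) on condition and three covariates: SCID-5 PTSD present or absent at baseline, "depression symptom severity (<15 or 15) assessed at baseline with the PHQ-9", and time since trauma split at 18 months. The last item is recorded with the PCL-5, but it is a date and not a severity score.

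These covariates are the "3 potential prognostic factors" used for minimisation (Sequence generation {21a and 21b}). That section explains that 15 is the pilot-study median PHQ-9 score among people with SCID-5 MDD, and that the upper group is 15 or more.

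Under Measures, Secondary outcome measures, PCL-5 and PHQ-9 totals are collected at baseline in both conditions. The secondary models include the same three factors "along with the baseline score of the measure being analysed".

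**The concern.** Recovery means meeting criteria for neither disorder at 8 weeks, so baseline severity of each is a natural candidate predictor. Within each PHQ-9 stratum the planned model treats all participants alike on depression severity. Within those who have PTSD it makes no severity distinction at all. A cut-point chosen to balance allocation need not be the form in which the variable enters the analysis: the continuous PHQ-9 score carries the same factor, uses the same number of parameters and keeps the within-stratum information. What is at stake is some power in the one confirmatory comparison, and some robustness of the estimate to chance differences in PTSD severity.

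**Working it through.** **1. The plan's own sample size.** Inputs from Sample size {19} and Trial design {12}: "calculated based on 90% power, at a significance level (*α*) of 0.05"; 50% against 84% not recovered; "two parallel conditions using a 1:1 allocation ratio". Two-sided test, pooled variance under the null, no continuity correction:

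n = [1.960 × √(2 × 0.67 × 0.33) + 1.282 × √(0.50 × 0.50 + 0.84 × 0.16)]² / 0.34² = (1.303 + 0.795)² / 0.1156 ≈ 38.1, so 39 per arm and 78 in total. Power at 39 per arm is 90.7%. With 15% attrition, 39 / 0.85 = 45.9, so 46 per arm and 92 in total. The plan's figures reproduce. The calculation is unadjusted, so it does not depend on the form of the covariates.

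**2. Recoveries available to support the model.** 39 × 0.50 + 39 × 0.16 = 19.5 + 6.2 ≈ 26. Recoveries per model term, intercept aside:
- planned model, 4 terms: 26 / 4 = 6.5
- split replaced by continuous PHQ-9, PCL-5 added, 5 terms: 26 / 5 = 5.2
- split kept and both scores added, 6 terms: 26 / 6 = 4.3

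**3. Effect of the covariate form on power.** Assumptions, none given by the documents: PHQ-9 and PCL-5 each shift the log-odds by the same amount per SD, their correlation is 0.5, the PHQ-9 split is at the median, marginal non-recovery is held at 84% and 50%, and arms are allocated at random in equal numbers (minimisation was not simulated). Likelihood-ratio test, 78 participants, 2,500 trials per row:

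| Log-odds per SD | Planned model | Continuous PHQ-9 replaces split, PCL-5 added | Split kept, both scores added |
|---|---|---|---|
| 0.0 | 91.0% | 91.1% | 90.7% |
| 0.3 | 91.7% | 92.0% | 91.8% |
| 0.5 | 92.0% | 93.2% | 93.2% |
| 0.8 | 94.5% | 95.9% | 95.9% |

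The Monte Carlo standard error of one entry near 92% is √(0.92 × 0.08 / 2500) ≈ 0.5 points. The replacement model gains about 0 to 1.5 points. With uninformative scores, the largest loss is 0.3 points, when the split is kept as well.

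A separate simulation (1,500 trials per setting, 78 participants) agrees. Likelihood-ratio power went from 90.9% to 90.8% with no prognosis, 94.5% to 95.9% at the middle setting and 95.9% to 97.1% at the strong setting. Wald power went from 89.9% to 89.8%, 93.3% to 95.1% and 94.1% to 95.7%. The largest gain is 95.1 − 93.3 = 1.8 points.

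**4. Type I error.** At 0.5 per SD and no treatment effect, rejection was 5.6% under both the planned and the continuous model.

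**5. Scale of a chance imbalance in PCL-5.** At 46 per arm its standard error is √(2/46) = 0.21 SD. If one SD shifts the log-odds by 0.6 (assumed), a two-standard-error imbalance moves the log odds ratio by 2 × 0.21 × 0.6 ≈ 0.25. That ignores the PCL-5 variation already captured by PTSD status and the PHQ-9 split. If 0.80 SD remains after those (also assumed), the shift is about 0.20, a factor of e^0.20 ≈ 1.22 on the odds ratio. For comparison, the planned log odds ratio is ln(0.84 / 0.16) = 1.66, with unadjusted standard error √(1/19.5 + 1/19.5 + 1/6.24 + 1/32.76) = 0.54 at 39 per arm.

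**The case against.** The strongest reply is that adjusting for exactly the factors used in allocation is a standard, pre-specified choice, and that a gain of under two points on power already near 90% is a matter of preference. This stands as far as validity goes, and it limits the point to a modest one.

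Three stronger readings are tempting, and the documents do not support them.

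- *The primary model contradicts the secondary ones.* It does not. The secondary rule adds the baseline value of the same measure. For the primary outcome that value is constant, because every participant starts with a diagnosis and scores 1.
- *Omitting PCL-5 biases the effect.* Chance imbalance under random allocation is not bias, and the confidence interval already allows for it. Minimising on PTSD presence and PHQ-9 group probably limits it further. Even the unlikely two-standard-error case in step 5 is under half of one standard error of the estimate.
- *The missing-at-random assumption is undermined.* Multiple imputation is foreseen above 5% missingness, and the article refers further detail to the statistical analysis plan, which was not available here. Whether baseline PCL-5 and PHQ-9 enter the imputation model cannot be judged.

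Two objections to the remedy have weight. Participants without PTSD rate the PCL-5 on their most stressful event (Sequence generation), so the score does not mean quite the same thing for everyone, and a single slope is an approximation. Recoveries per term are also few. Neither defeats the change: PTSD status stays in the model, and the simulations show no meaningful loss at this sample size.

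**Conclusion.** The point holds as a modest weakness in efficiency. The primary model is valid, and the sample size stands. Using the two continuous scores would add about 0 to 2 points of power, depending on prognostic strength, which the documents do not give and which was assumed from 0 to 0.8 log-odds per SD. It would also reduce the estimate's exposure to chance differences in PTSD severity. The change is worth making because the data are already to be collected and the cost is small. The result would not be unsafe without it.

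**What to change.** In Main trial analyses, Primary outcome: keep SCID-5 PTSD presence and time since trauma, enter baseline PHQ-9 as a continuous score (in place of the split at 15, or alongside it), and add the continuous baseline PCL-5 total. Report the model with the minimisation factors only as a sensitivity analysis.

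The cost is a line of wording and one extra parameter (two if the split is kept), against about 26 expected recoveries. No new data are needed. The two models' odds ratios condition on different covariates and can differ for that reason alone, so the report should say so.

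Timing decides which version applies. The article gives recruitment as complete, had expected it to end in mid-November 2024, and is dated October 20, 2025. It plans an analysis once all available 8-week data are in, and does not say whether that has been run. If the 8-week data have already been analysed by arm, the planned model should remain primary and the model with continuous scores be reported as supportive and labelled as added later.

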##### Secondary outcomes

All secondary outcome analyses will be treated as exploratory analyses.

Between-group analyses of the continuous secondary outcome measures will include mixed effects regression models and multiple regression models following the same specifications as the primary outcome measure with additional fixed effects for time, a time by condition interaction, and a random effect for participant for the mixed-effect regression models. Mixed effects regression models allow for the inclusion of all available data from randomised participants (ITT), can account for missing data, and can account for repeated measures [67]. Between-group effect sizes (Cohen’s *d*) will be calculated by dividing the adjusted group difference by the baseline standard deviation.

For secondary outcome measures collected at 4 and 8 weeks post-random allocation (i.e. PCL-5, PHQ-9, GAD-7, PTCI-s, and RIQ-s), statistical models of treatment effects will include categorical fixed factors of time (4 weeks, 8 weeks post-random allocation), condition (SHAPE, waitlist), and the time × condition interaction. The interaction permits the estimation of differences between treatments at each timepoint. Participant will be treated as a random effect to account for between-participant variation.

For secondary outcome measures collected at 8 weeks post-random allocation only (i.e. ISI, ITQ, WEMWBS, CD-RISC, and social support scales), we will fit multiple regression models including condition (SHAPE, waitlist).

The stratification variables absence/presence of PTSD assessed with the SCID-5 at baseline, depression symptom severity (<15 or 15) assessed at baseline with the PHQ-9, and time since reported trauma (>/<18 months) assessed at baseline with the PCL-5 will be included as fixed covariates, along with the baseline score of the measure being analysed. Significance level will be set to *p* < 0.05 for comparison between the SHAPE and waitlist conditions.

To assess for potential correlates of PTSD and MDD symptom change, we will conduct correlational analyses to assess the strength of the relationship between change in posttraumatic cognitions and maladaptive responses to intrusions from baseline to week 4, and from baseline to week 8 and change in PTSD and MDD symptom severity over the same time periods, controlling for baseline scores on these measures. This analysis will be conducted with the whole sample at week 8 to include post-intervention and post-wait participants.

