For the dichotomous secondary outcome measure, SCID-5 diagnosed PTSD and MDD at 6 months post-intervention completion, a mixed effects logistic regression model will be used. For the between-group analysis, the model will include fixed factors of time (post-intervention, 6-month post-intervention completion), condition (SHAPE, waitlist), and time × condition. Participant will be treated as a random effect. If there is not a significant difference between groups (receiving SHAPE immediately or after waitlist), a within-group analysis will be conducted that will include fixed factors of time (post-intervention, 6-month post-intervention completion), and participant will be treated as a random effect. If there is a significant difference between groups, separate within-group analyses will be conducted for each condition. The stratification variables absence/presence of PTSD based on the SCID-5, depression symptom severity (<15 or 15) based on the PHQ-9, and time since trauma (>/<18 months) based on the PCL-5 will be included as fixed covariates in all models, along with the pre-intervention diagnosis of PTSD and MDD.

For the continuous secondary outcome measures collected at 6 months post-intervention completion, mixed effects regression models will be used. For the between-group analyses (receiving SHAPE immediately or after waitlist), models will include fixed factors of time (post-intervention, 6-month post-intervention completion), condition (SHAPE, waitlist), and time × condition. Participant will be treated as a random effect. If there is not a significant difference between groups, within-group analyses will be conducted that will include fixed factors of time (post-intervention, 6-month post-intervention completion), and participant will be treated as a random effect. If there are significant differences between groups, separate within-group analyses will be conducted for each condition. The stratification variables absence/presence of PTSD based on the SCID-5, depression symptom severity (<15 or 15) based on the PHQ-9, and time since trauma (>/<18 months) based on the PCL-5 will be included as fixed covariates in all models, along with the pre-intervention score of the measure being analysed.

A detailed statistical analysis plan is available to view as a supplementary file.

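### For the five measures modelled at weeks 4 and 8, the week-8 between-group standard error is valid only if the baseline-adjusted variance is equal at both weeks

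*Protocol article*

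**What the plan says.** Under Main trial analyses, Secondary outcomes, the protocol article names five measures collected at both weeks 4 and 8: PCL-5, PHQ-9, GAD-7, PTCI-s and RIQ-s. Their model has "categorical fixed factors of time (4 weeks, 8 weeks post-random allocation), condition (SHAPE, waitlist), and the time × condition interaction", plus the three stratification variables and the baseline score. On the purpose of the interaction it says: "The interaction permits the estimation of differences between treatments at each timepoint". The only variance component named is the participant effect: "Participant will be treated as a random effect to account for between-participant variation". Nothing is said on whether the residual variance may differ between the two weeks.

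Measures taken at week 8 only are handled differently: "we will fit multiple regression models including condition (SHAPE, waitlist").

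The same section sets the status and the threshold: "All secondary outcome analyses will be treated as exploratory analyses", and "Significance level will be set to *p* < 0.05 for comparison between the SHAPE and waitlist conditions".

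Follow-up analyses uses the same structure for post-intervention and 6 months: "For the continuous secondary outcome measures collected at 6 months post-intervention completion, mixed effects regression models will be used", again with participant as the only random effect. A between-group comparison at 6 months decides whether the two arms are pooled for the within-group analyses.

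**The concern.** With two records per person, a participant random intercept and a single residual variance imply equal total variance on both occasions. The within-person correlation is still estimated freely, provided it is positive, so equal variance is the only added restriction. It matters because the Hypotheses section places the symptom predictions at week 8, and the model is meant to deliver a treatment difference at that week. If the adjusted variance is larger at week 8 than at week 4, the week-8 interval is too narrow and the 5% test rejects too often. If it is smaller, the interval is too wide and power is lost.

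The relevant variance is the one left after baseline adjustment. Equal raw SDs at the two weeks are therefore not enough; the correlation with baseline must be equal too. The section is also uneven: the ISI, ITQ and WEMWBS get a week-8 standard error from week-8 data alone, while the PCL-5 and PHQ-9, the symptom-severity measures named in the abstract, do not.

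**Working it through.** **The plan's own figure.** The article gives no SD, standard error or power for these outcomes, so there is nothing on this point to reproduce. The group size used below comes from Sample size: 50% against 16% recovery, 90% power, two-sided 5% (assumed). With the pooled-variance formula, n = (1.96·√(2·0.33·0.67) + 1.2816·√(0.25 + 0.1344))² / 0.34² = 38.1, so 39 per arm; 39/0.85 = 45.9, so 46 per arm and N = 92. This agrees with the article but does not bear on the point.

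**Week-8 contrast, complete data.** Let s4 and s8 be the baseline-adjusted SDs and r = s8/s4.

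- True variance of the week-8 difference: 2·s8²/n.
- Variance reported by the model: 2·[(s4² + s8²)/2]/n.
- Model SE / true SE = √((1 + 1/r²)/2).
- Actual type I error = 2·Φ(−1.96 × that ratio).

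For r = 1.2: (1 + 0.694)/2 = 0.847, square root 0.920, 1.96 × 0.920 = 1.80, type I error 7.1%.

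| r (assumed) | SE ratio | Type I error | Coverage of 95% interval |
|---|---|---|---|
| 0.8 | 1.132 | 2.7% | 97.4% |
| 0.9 | 1.057 | 3.8% | 96.2% |
| 1.0 | 1.000 | 5.0% | 95.0% |
| 1.1 | 0.956 | 6.1% | 93.9% |
| 1.2 | 0.920 | 7.1% | 92.9% |
| 1.3 | 0.892 | 8.0% | 92.0% |
| 1.5 | 0.850 | 9.6% | 90.4% |

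**Simulation check.** A REML random-intercept model was fitted with 39 per arm, an assumed residual correlation of 0.6 and 400 replicates per case (Monte Carlo error about 1 to 1.6 points). Type I error was 3.0% (r = 0.8), 4.3% (1.0), 6.3% (1.2) and 8.8% (1.5). With 15% missing at week 8 it was 8.3% (r = 1.2) and 11.0% (r = 1.5). A week-8-only regression, as a proxy for a week-specific variance, gave 4.0 to 5.0% with complete data, and 4.8% and 6.5% with 15% missing.

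**What could move r away from 1.** The adjusted SD is SD·√(1 − ρ²), where ρ is the correlation with baseline. All values here are assumptions.

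- Raw SDs 15 and 15, ρ 0.7 then 0.5: 10.71 and 12.99, r = 1.21; simulated type I error 7.0%.
- Raw SDs 17 then 14, ρ 0.7 then 0.5: 12.14 and 12.12, r = 1.00; simulated 5.2%, no distortion.
- Raw SDs 17 then 14, equal ρ at both weeks: r = 14/17 = 0.82; simulated 3.2%.

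**Contrasts that are not exposed.** With two occasions and complete data, the residual variance is estimated from within-person differences. Tests of time and of time × condition therefore rest on the variance of the difference itself, as in a paired analysis, whatever the two variances are. In simulation they held at 4.9–5.4% (time) and 4.6–5.4% (interaction).

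**The case against.** The strongest reply is that the article names a participant random effect and stops. Such an effect can be combined with time-specific residual variances, and residual covariance and degrees of freedom are commonly left to the SAP, which the article cites and which is not shown. This stands as a limit: the article does not rule out a correct fit. It does state a model, however, and the ordinary fit of that model carries the restriction.

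A reader might infer that the week-8 p-values and intervals are wrong, or too liberal. The documents do not support that. They give no SD or correlation for any of the five measures. Residual variance may grow as correlation with baseline decays and responses diverge. It may also shrink: the scales are bounded at zero and half the SHAPE arm is expected to recover. The section on changed recall periods does not settle it. Read literally, it gives the PCL-5 and PHQ-9 a past-week window in weeks 1–7 and the standard window at baseline, so their correlation with baseline need not fall from week 4 to week 8.

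A reader might also carry the point to the follow-up conclusions or the main trial result. Neither follows. The within-group time effects under Follow-up analyses are unaffected with complete data. The primary outcome is a logistic regression at one timepoint and does not use this model.

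Finally, these analyses are declared exploratory, and a random intercept is a standard choice for two occasions. Both are true and keep the point small.

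**Conclusion.** The point holds in conditional form. As usually fitted, the stated model gives a correct week-8 between-group standard error for the five measures only if the baseline-adjusted variances at weeks 4 and 8 are equal. For r between 0.9 and 1.2 the nominal 5% test lies between 3.8% and 7.1%; at r = 0.8 it is 2.7% and at r = 1.3 it is 8.0%. These figures assume complete data, a two-sided test and a large-sample normal approximation. The value of r is an assumption throughout, so neither the existence nor the direction of an error is shown.

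Only the between-group contrast at a single occasion is exposed: week 8 in the main analyses, and the 6-month contrast where it serves as the test for pooling the arms. With complete data the treatment estimates, the within-group time tests and the time × condition tests are unaffected. The primary analysis and the week-8-only regressions do not use this model. This is a low-cost improvement to exploratory analyses, not a threat to the trial's main result.

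**What to change.** In Secondary outcomes and in Follow-up analyses, for continuous measures with two modelled occasions, replace the single participant random effect by a repeated-measures model with an unstructured 2×2 covariance (a variance for each occasion and their covariance). Add a baseline × time term (pre-intervention score × time in the follow-up models), and use Kenward-Roger or Satterthwaite degrees of freedom. Report the week-8 contrast, and the 6-month between-group contrast, from that model. If the SAP already allows the variance to differ by occasion, one sentence in the article saying so is enough.

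The cost is one extra variance parameter and one interaction term per outcome, and slightly wider week-8 intervals if the variance does rise. No new data are needed, and the model keeps the use of all available records under the missing-at-random assumption.
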